### Statistical analysis

Data will be analyzed at the individual (patient) level. Statistical analyses will be performed using the intention-to-treat (ITT) approach in the originally assigned groups. Demographic and baseline characteristics for the intervention and control groups will be presented in the form of mean (standard deviation (SD)) or 95% confidence intervals (CIs) for continuous variables and counts (percentages) for categorical variables. ITT analysis will be performed on the final data collected at 12 months.

Generalized estimating equations (GEEs) with clustering by site, an exchangeable correlation matrix and robust variances will be used to assess the program effect adjusting for potential baseline covariates. The model will take account of clustering and will be used to look at the difference between groups for the HbA1c level at 6 and 12 months, respectively. Multiple imputation will be used to account for the missing values assuming they are missing at random. To test for the secondary sensitivity analysis, data will be analyzed without multiple imputation and without baseline covariate adjustment. The difference in the incidence of diabetes between the groups among the individuals with prediabetes will be tested using a GEE. Statistical significance will be assessed at the 5% level and all analyses will be two-sided. All data analyses will be performed using the Stata 15 (StataCorp, TX, USA) statistical software program.

As we expect that the program effect may differ between several subgroups of the program participants, we plan to do secondary analyses of the following three subgroups for the primary (HbA1C) and secondary (incidence of diabetes) outcomes: the subgroups with poor initial glycemic level (HbA1c ≥ 5.7%) (people with poorer glycemic level at baseline may have a stronger desire to change their behavior); the subgroups divided by gender (in Nepal, women tend to be more adherent to clinician guidance); the subgroups of different social economic classes (people in higher socioeconomic class may be more likely to adhere to lifestyle changes); and government versus nongovernment health centers. The secondary analyses will compare the HbA1c level and incidence of diabetes among people with prediabetes among these subgroups at the end of the 12-month intervention using the generalized linear mixed models with a random cluster effect and adjusting for potential confounders.

Descriptive statistics (i.e., counts, means and proportions) will be calculated to evaluate the reach, effectiveness, adoption and implementation of the program.

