### Setting

The study will be conducted in 26 clusters: 9 outreach centers (Bahunepati, Manekharka, Hindi Health, Baluwa, Bolde Phediche, Dapcha, Kartike Deurali, Salambu and Dhunkharka Health Centers) of Dhulikhel Hospital, Kathmandu University Hospital and 17 government health posts located in the adjoining catchment areas purposively selected from the Kavrepalanchowk and Sindhupalchowk districts. The primary stratification variable, as well as the unit (cluster) of randomization and implementation, will be health clinics (outreach centers and health posts (HPs)). There will be 13 clusters per treatment arm (1:1 allocation ratio). Outreach centers are the small medical health facilities that offer basic and emergency care services in remote areas of Nepal. These centers are run by Kathmandu University Hospital. Similarly, health posts are government-run facilities that provide basic health care and preventive medication in remote rural areas of Nepal.

Kavrepalanchowk district located in Province 3 of Nepal consists of 13 municipalities: 6 urban and 7 rural municipalities with a total of 137 wards. The headquarter of this district is Dhulikhel municipality. A total population of 381,937 resides in this district; 62.51% live in the urban municipalities and 37.49% live in the rural municipalities. There is one 15-bed district hospital, 4 primary health care (PHC) centers and 86 HPs in the district [10]. Sindhupalchowk district, also located in Province 3 of Nepal, consists of 12 municipalities: 3 urban and 9 rural municipalities with a total of 103 wards. The headquarter of Sindhupalchowk district is Chautara. A total population of 287,798 resides in this district; 41.42% live in the urban municipalities and 58.58% live in the rural municipalities. There is one 15-bed district hospital, 3 PHC centers and 75 HPs in the district [10]. The maps of Kavrepalanchowk and Sindhupalchowk districts with the distribution of outreach centers and health posts are shown in Figs. 2 and 3.

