### Randomization

The 26 health clinics will be randomized 1:1 into the continuum of care group (intervention) and the usual care group (control), stratified by outreach center and health post. The usual care group includes those who continue managing their diabetes under the direction of their primary care providers, which is the most commonly used method for diabetes management in Nepal. The selection of the usual care group as a comparator is thus justified. A statistician otherwise not involved in the project will perform this group assignment at the cluster level with simple random selection with the R statistical program. Randomization will be done before participant recruitment. Outcome assessors will be blinded to the group assignment, but the nurses and patient participants will be aware of their group assignment. If blinding to the outcome assessor is accidentally broken, they will follow a standard protocol for reassessment of the patients at another time. Any violations of the study protocol will be recorded and reported to the Ethics Committee.

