### Sample size

In this proposed community-based intervention, changes in the HbA1c levels (continuous outcome) were considered for calculating the sample size for the individuals with diabetes and the incidence of diabetes (binary outcome) was considered for calculating the sample size for the individuals with prediabetes, respectively. For the individuals with diabetes, we aim to detect a clinically significant reduction in HbA1c levels from 7.6% to 6.5% (SD = 1.5%) (based on our assumption, the recommended effective diabetic management level and results of previous studies) among the individuals with diabetes during the 12-month period [35, 36] with medium effect size [37]. We expect a reduction of HbA1c to 7.0% in the control group, an optimal target level defined by the American Diabetes Association (ADA) [38]. Setting the statistical significance at the 0.05 level, seeking 90% power, with an intraclass correlation coefficient (ICC) of 0.01 based on a previous study conducted in Nepal [39], an average cluster size of 50 (individuals with diabetes) based on preliminary data from the awareness and screening campaign, a design effect for clustering of 1.49 and a design effect for unequal cluster size of 1.52 (coefficient of variation of cluster size 0.25), 91 people with diabetes per arm (182 total) will be required for the study. For the incidence of diabetes among people with prediabetes (dichotomous outcome), we considered the incidence of 10% and 2%, respectively, for the two groups; stated as a range in an earlier study [40]. Based on these considerations, 471 people with prediabetes per arm (942 total) will be required. We expect a dropout rate of 10% from baseline to 12-month follow-up; hence, we will need to recruit a total of 200 diabetes and 1036 prediabetes participants (total sample size = 1236 participants). The sample size for our cluster RCT was calculated using the following equation. Details of the sample size estimation is available in another study conducted by Ribeiro et al. [41]:

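### With only 26 clusters, the stated GEE with robust variances runs at about 7–8% two-sided error for HbA1c, not 5%, unless a small-sample correction is specified

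*Protocol article*

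**What the plan says.** The Statistical analysis section of the protocol article fixes the analysis of the program effect: "Generalized estimating equations (GEEs) with clustering by site, an exchangeable correlation matrix and robust variances will be used to assess the program effect". The part of that sentence on covariates reads only "adjusting for potential baseline covariates", and the covariates are not listed there. This model is tied to HbA1c at 6 and 12 months. Diabetes incidence among people with prediabetes is to be tested by a GEE, and neither the working correlation nor the variance is repeated. The level is explicit: "Statistical significance will be assessed at the 5% level and all analyses will be two-sided".

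The number of independent units comes from the Setting section: "The study will be conducted in 26 clusters: 9 outreach centers" and 17 government health posts. "There will be 13 clusters per treatment arm (1:1 allocation ratio"). Under Randomization, allocation is "stratified by outreach center and health post".

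The article names no small-sample variance correction, t or F reference, permutation test or cluster-level analysis. The sensitivity analyses drop multiple imputation and covariate adjustment, and nothing says that they change the variance estimator.

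**The concern.** The robust (sandwich) variance is justified by a large number of clusters. More participants per cluster do not help. With 13 clusters per arm two things go wrong in the same direction. The estimated variance is too small on average, because residuals from a fitted model are smaller than the true errors. The variance estimate is also itself noisy, which a normal reference ignores. P-values are then too small and confidence intervals too narrow. For a program meant to inform policy, the primary test would reject a true null more often than the stated 5%. The planned sensitivity analyses would not reveal this if they keep the same variance.

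**Working it through.** **Inputs from the protocol.** K = 26 clusters, 13 per arm, in strata of 9 and 17 (Setting, Randomization); ICC 0.01, cluster-size coefficient of variation (cv) 0.25 and SD 1.5 (Sample size); 5% two-sided (Statistical analysis). The plan gives "seeking 90% power, with an intraclass correlation coefficient (ICC) of 0.01 based on a previous study conducted in Nepal" and "an average cluster size of 50 (individuals with diabetes").

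**The plan's own sizes.** They reproduce as 40 × 1.49 × 1.52 = 90.6, so 91 per arm with diabetes, and 208 × 1.49 × 1.52 = 471.1, so 471 per arm with prediabetes. The required totals imply 182/26 = 7 people with diabetes and 942/26 ≈ 36 with prediabetes per cluster, not 50. Both 7 and 50 were therefore tried for HbA1c.

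**Closed-form check (equal clusters, arm only).** The sandwich variance has expectation 12/13 of the true variance and carries 24 degrees of freedom.

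- Plain sandwich, normal reference: P(|t24| > 1.96 × √(12/13)) = 7.2%.
- With K/(K−1) scaling: 12/13 × 26/25 = 0.96, so P(|t24| > 1.96 × √0.96) = 6.7%.
- With the stratum added, approximating the variance ratio as 23/26 on 23 degrees of freedom: P(|t23| > 1.96 × √(23/26)) = 7.8%.

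None of these uses the ICC or the cluster size.

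**Simulation under the null.** Stratified allocation, exchangeable GEE, cv 0.25, ICC 0.01, 4,000 runs per row (simulation error about 0.4 points). Entries are % rejected; KC is Kauermann-Carroll and MD is Mancl-DeRouen.

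| Outcome, mean per cluster | Model | Sandwich, z | × K/(K−1), z | Sandwich, t(24) | KC, t(24) | MD, t(24) |
|---|---|---|---|---|---|---|
| HbA1c, 7 | arm | 7.4 | 6.8 | 6.0 | 4.7 | 3.8 |
| HbA1c, 7 | + stratum | 8.2 | 7.7 | 6.9 | 5.0 | 3.6 |
| HbA1c, 7 | + stratum, 3 individual covariates | 8.9 | 8.5 | 7.7 | 6.0 | 4.3 |
| HbA1c, 50 | arm | 7.0 | 6.6 | 5.7 | 4.8 | 4.0 |
| HbA1c, 50 | + stratum | 8.2 | 7.6 | 6.8 | 5.2 | 3.9 |
| HbA1c, 50 | + stratum, 3 individual covariates | 8.0 | 7.4 | 6.7 | 5.3 | 4.3 |
| Incidence 6%, 36 | arm | 7.1 | 6.5 | 5.5 | 4.7 | 3.8 |
| Incidence 6%, 36 | + stratum | 8.2 | 7.6 | 6.8 | 5.5 | 4.1 |
| Incidence 6%, 36 | + stratum, 3 individual covariates | 8.2 | 7.7 | 7.0 | 5.3 | 3.8 |

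Across all 14 scenarios at cv 0.25, including ICC 0.05 and null incidence of 2% and 10%, the plain sandwich with z ranges from 7.0% to 8.9%. A separate set of runs gave 6.4–8.1%. A t(24) reference on the uncorrected variance still gives 5.5–7.7%, so changing the reference alone is not enough.

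**Check of the recommended degrees of freedom.** With the stratum in the HbA1c model, t(23) and 8,000 runs, Kauermann-Carroll gives 5.3% at 7 per cluster and 5.6% at 50. Mancl-DeRouen gives 3.7% and 4.0%.

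**If cluster sizes vary more.** At cv 0.6 with the stratum and t(24), the plain sandwich with z gives 11.3% (HbA1c, 7 per cluster) and 9.3% (incidence). Kauermann-Carroll gives 7.0% and 5.9%, and Mancl-DeRouen 4.2% and 3.8%.

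**Price in interval width (arm only).** Kauermann-Carroll: √(13/12) × 2.064/1.96 = 1.10. Mancl-DeRouen: (13/12) × 2.064/1.96 = 1.14. The same approximation with the stratum and t(23) = 2.069 gives √(26/23) × 2.069/1.96 = 1.12 and (26/23) × 2.069/1.96 = 1.19.

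**The case against.** The strongest reply is that robust variances name a family. Kauermann-Carroll and Mancl-DeRouen are themselves robust variances, so the recommended method is compatible with the printed wording. A journal article often leaves the correction and the reference distribution to a statistical analysis plan, which is not shown here. This stands in part: a reader might infer that the trial will certainly be analyzed without a correction, and the document does not establish that. But the article goes as far as naming the estimator, the level and the number of clusters, and the ordinary reading of that combination misses 5%. An analysis written from this text would inherit the problem.

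Three other inferences go further than the text.

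- **That the same method is stated for both primary outcomes.** It is explicit only for HbA1c; for incidence it is a natural assumption.
- **That the error climbs further as site-level covariates are added.** The Baseline assessment section lists individual characteristics, and the protocol proposes no site-level covariate for the model. The stratum is neither included nor excluded by the open covariate wording.
- **That adjusting for baseline HbA1c would repay the wider intervals.** No baseline-to-follow-up correlation is given, and baseline adjustment is already planned in general terms, so no offset can be shown.

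It is also fair to say that the simulations contain no missing data, whereas the planned primary analysis uses multiple imputation.

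**Conclusion.** The concern holds in a conditional form. Taken as the standard sandwich with a normal reference, the stated HbA1c analysis has a true two-sided error of about 7–8%. This rises to about 9% with the stratum and a few individual covariates, and is about 6–8.5% with K/(K−1) scaling. The same holds for incidence only if its GEE has the same set-up. The excess is about 2–4 percentage points and comes from the 26 clusters rather than from a particular ICC or cluster size. The figures rest on complete data, assumed individual covariates and the protocol's cv of 0.25; greater imbalance in cluster size makes them worse. The exact rate under the full planned analysis, with imputation, has not been computed.

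**What to change.** For both primary outcomes, state the following in the analysis section:

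- GEE with exchangeable correlation, clustered by site, with one named small-sample-corrected robust variance. Use Kauermann-Carroll, or Mancl-DeRouen if cluster sizes vary much more than cv 0.25. Fix the choice before outcomes are compared by arm.
- A t reference with 26 minus the number of cluster-level parameters: intercept, arm and stratum, so 26 − 3 = 23 degrees of freedom.
- The randomization stratum (outreach center or health post) in the model, plus baseline HbA1c for the HbA1c outcome. Baseline HbA1c is individual-level and does not reduce the 23.
- The same variance and reference for the sensitivity analyses.

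The cost is wording and a GEE routine that provides the correction. Relative to the uncorrected analysis, intervals widen by about 10% with Kauermann-Carroll or 14% with Mancl-DeRouen in the arm-only approximation, and by about 12% or 19% with the stratum. Mancl-DeRouen also gives up some level, at about 3.4–4.3% in these scenarios. Design and data collection do not change, and the Trial status section says recruitment had not begun.

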#### Eligibility criteria for participants

To resemble the real-world settings as much as possible, we will apply the minimum inclusion and exclusion criteria for the participants. Individual with confirmed pre-existing type II diabetes and prediabetes at the time of our screening (i.e., pre-existing diabetes or prediabetes) or with a confirmed diagnosis of type II diabetes or prediabetes after our community screening process (i.e., newly diagnosed diabetes and prediabetes), who is not planning to relocate outside the current place of living in next 2 years and is older than 18 years of age, will be eligible for project recruitment. People will be excluded if they: are not psychologically capable of communication; and are diagnosed with type 1 diabetes. Participants will be assessed for the risk of diabetes using the Indian Diabetes Risk Score (IDRS) [11]. Anyone identified as at risk will undergo a random finger-prick glucose test followed by the hemoglobin A1c (HbA1c) test. The diagnosis will be confirmed by an HbA1c level ≥ 6.5% for diabetes or between 5.7 and 6.4% for prediabetes [12].

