Recruitment will be primarily through conducting diabetes awareness mass campaigns in the targeted sites of the two districts to achieve adequate participant enrollment. We intend to reach 50,000 people (approximately 2000 people at each of the 9 outreach centers and 17 health posts). Interested candidates will contact the study nurses, who will provide them with basic information about participation, including information on the screening process, time commitment and expectations associated with participation. Assuming 25% of those who are made aware of diabetes will participate in the screening (see later for the details of screening methods), we target screening 12,500 participants. The two-step screening approach will be used for the study after assessing the risk of diabetes among the individuals using the IDRS assessment tool. In the first step, anyone under risk will undergo a random finger-prick blood glucose test using Beurer glucometers [13]. A random blood sugar level of 200 mg/dl or higher will be considered positive for diabetes and a sugar level of 140–199 mg/dl will be considered positive for prediabetes [12]. In the second step, participants screened positive for a random blood glucose level will undergo a glycosylated hemoglobin (HbA1c) test. An HbA1c level between 5.7 and 6.4% will be considered positive for prediabetes and an HbA1c level of 6.5% or above will be considered positive for diabetes [12]. Participants with HbA1c level ≥ 5.7% will be invited to participate in the study. Based on the earlier quoted prevalences of 8.4% (95% CI: 6.2–10.5%) for diabetes [1] and 13% (95% CI: 11.8–14.5%) for prediabetes [14], we expect to identify 1050 (12,500 × 0.084) individuals with diabetes and 1625 (12,500 × 0.13) individuals with prediabetes for this study.

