### Outcome measures

We will examine both clinical outcomes and implementation outcomes as we hypothesize that the nurse-led continuum of care program will improve both health and the implementation of priority interventions in diabetes. The outcome measure will pertain to the individual participant level. The primary outcome for the diabetes group is the HbA1c level at 12 months from the intervention. The HbA1c level is indicative of the average level of blood glucose over the past 2–3 months [22]. The primary outcome for the prediabetes group is the incidence of diabetes at 12 months from the intervention.

The secondary outcomes are blood pressure, body mass index (BMI) and lipid levels. Also, the secondary outcomes include a series of implementation outcomes in the RE-AIM (reach, effectiveness, adoption, implementation, and maintenance) implementation framework [23–25]. We provide details on those measures in the following (see Table 2 for a summary).

**Table 2 Tab2:** Measures of outcome variables

	Assessment method	Assessor	Baseline	Midline (6 months)	End line (12 months)	Variable

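### The baseline-HbA1c subgroup is cut at the trial's own entry threshold, so it holds all or nearly all participants and cannot show whether the program effect varies with baseline glycemia

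*Protocol article*

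**What the plan says.** The subgroup paragraph of the Statistical analysis section opens with its purpose: "As we expect that the program effect may differ between several subgroups of the program participants". It then lists four factors: baseline glycemic level, gender, socioeconomic class, and government versus nongovernment facility. The first is given as "the subgroups with poor initial glycemic level (HbA1c ≥ 5.7"%), on the reasoning that people with poorer glycemia may be more motivated to change. The analyses, by generalized linear mixed model with a random cluster effect, "will compare the HbA1c level and incidence of diabetes among people with prediabetes among these subgroups" at 12 months.

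Two earlier sections fix who can be in the trial. Screening and recruitment states: "Participants with HbA1c level ≥ 5.7% will be invited to participate in the study". Eligibility criteria for participants states: "The diagnosis will be confirmed by an HbA1c level ≥ 6.5% for diabetes or between 5.7 and 6.4% for prediabetes". The eligibility section also admits an "Individual with confirmed pre-existing type II diabetes and prediabetes at the time of our screening", and that sentence attaches no HbA1c value.

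**The concern.** A subgroup analysis needs people on both sides of the dividing line. Here the line is the entry threshold, so the subgroup meant to pick out poorer baseline control picks out the trial population. The analysis would then repeat the main result under a subgroup label and could be read as evidence about poorly controlled participants when it is not.

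There is a lesser mismatch in the same paragraph. The aim is to see whether the program effect differs between subgroups, but the sentence describing the analysis compares outcomes among subgroups and names neither an arm contrast nor an interaction. Taken literally, that is a prognostic comparison, such as women against men, and it does not address the stated aim.

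**Working it through.** The plan gives no figure for the size of this subgroup, so there is none to reproduce. The check sets the cut-offs side by side and then asks how far the one possible exception could rescue the analysis.

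**Step 1: cut-offs.**
- Subgroup (Statistical analysis): HbA1c at or above 5.7%.
- Invitation to the trial (Screening and recruitment): HbA1c at or above 5.7%.
- Prediabetes diagnosis (Eligibility criteria): 5.7 to 6.4%, all of it at or above the cut-off.
- Diabetes diagnosis (Eligibility criteria): 6.5% or above, so it starts 6.5 − 5.7 = 0.8 points above the cut-off.

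**Step 2: subgroup share under the invitation rule.** Planned enrolment (Sample size section) is 200 + 1036 = 1236. The share in the subgroup is 200/200 in the diabetes cohort, 1036/1036 in the prediabetes cohort and 1236/1236 overall. The complement is 0 people.

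**Step 3: what a share f does to precision.** Let V be the variance of the arm effect estimated in everyone. With equal residual variance, arms balanced within subgroups and clustering ignored, the two subgroup effects have variances V/f and V/(1 − f). The variance of their difference is V × [1/f + 1/(1 − f)].
- f = 0.50: 2 + 2 = 4 times V.
- f = 0.90: 1.11 + 10 = about 11 times V.
- f = 0.99: 1.01 + 100 = about 101 times V.
- f = 1: unbounded, so the interaction cannot be estimated.

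**Step 4: the pre-existing route.** Suppose the invitation rule does not bind people with pre-existing diabetes. As an assumption, let all 200 diabetes participants enter that way, with HbA1c normal at the planning mean of 7.6% and SD of 1.5% (Sample size section). Then:
- z = (5.7 − 7.6)/1.5 = −1.27, and the probability below 5.7% is 0.103.
- Number below 5.7%: 200 × 0.1026 = 20.5, about 21 people.
- Share of the whole trial: 20.5/1236 = 1.7%.

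The complement in the diabetes cohort therefore ranges from 0 to about 21. At that upper end f is about 0.90, and the standard error of the interaction is √11.1 = 3.3 times that of the overall effect, against √4 = 2 times for an even split. For screen-detected prediabetes the complement is 0 by definition. For pre-existing prediabetes the document gives no HbA1c distribution, so no number can be attached.

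**The case against.** **The 100% figure.** The eligibility sentence on pre-existing disease has no HbA1c floor, so a treated person could present below 5.7%. This stands as a qualification: all or nearly all is the safe wording. It does not rescue the analysis. The Screening and recruitment section describes recruitment as community screening followed by the 5.7% invitation rule, and even the generous assumption in the working leaves a small comparison group.

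**The comparison among subgroups.** A reader might infer that the gender, socioeconomic and facility analyses will report differences unrelated to treatment. The document does not support that as a certainty. The paragraph opens with differing program effects, its rationales concern response to the program, and the wording can be read as arm contrasts within subgroups. Interaction terms are also commonly left to a statistical analysis plan, which is not shown. What stands is that the sentence as written does not match its aim and needs clarifying.

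**The outcome label.** The subgroup paragraph plans its analyses "for the primary (HbA1C) and secondary (incidence of diabetes) outcomes", while Outcome measures states: "The primary outcome for the prediabetes group is the incidence of diabetes at 12 months from the intervention". A reader might infer that the confirmatory outcome for the prediabetes cohort is left open. It is not: the Abstract, Outcome measures and Table 2 all make incident diabetes primary, and the Sample size section sizes the prediabetes cohort on it. The label is a slip. So is the announcement of three subgroups where four are listed.

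**The model.** A mixed model with a random cluster effect is a valid clustered analysis for secondary questions. Nothing in the document requires it to be replaced by the GEE used for the main analysis.

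**Conclusion.** The point holds for the baseline glycemic subgroup. Its cut-off equals the entry threshold, so it contains everyone under the invitation rule and nearly everyone if pre-existing cases may enter lower: a complement of 0 to about 21 of 200 in the diabetes cohort, the upper figure resting on assumed normality at the planning mean and SD and on all 200 entering by that route. Effect modification by baseline glycemic level cannot be estimated in the first case and would be very imprecise in the second.

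The defect affects one of four secondary subgroup analyses. It changes no primary estimate, sample size or primary conclusion. The wording of the other three calls for clarification, and the outcome label and the subgroup count are editorial. It should be corrected because the cut-off is wrong as written, and an analysis plan that carried it over would inherit the fault.

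**What to change.** In the subgroup paragraph:

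1. Replace the 5.7% subgroup with an arm-by-baseline-HbA1c interaction, fitted separately in the diabetes and prediabetes cohorts. Use HbA1c as a continuous variable, or a cut-off that divides each cohort, to be chosen by the investigators. Fitting within cohorts matters because the two cohorts have different primary outcomes and are themselves separated by HbA1c.
2. State that the gender, socioeconomic and facility-type analyses test the arm-by-subgroup interaction and report the arm effect with a confidence interval at each level. The stated mixed model can stay.
3. Editorial: reconcile the secondary label for incident diabetes with the Abstract, Outcome measures and Table 2, and reconcile the count of three subgroups with the four listed.

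The cost is one paragraph of wording. Baseline HbA1c is already measured in every participant, and the Trial status section says recruitment had not begun, so the change can be made before any outcome data exist.
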